#### 4.4 Sample size calculation

Subject to safety and tolerability we aim in these studies to achieve a 100% infection rate in 10 subjects. At a lower infection rate of 80% (for example) this sample size will estimate attack rate with precision of approximately  $\pm 22.5\%$ ; i.e. ruling out an attack rate of less than 50%. For future vaccine proof-of-concept efficacy studies, small groups of roughly 10 subjects are generally preferred, allowing for detection of roughly ~50% protective vaccines with a power of 80% ( $\alpha < 0.05$ , 2-tailed). A 100% attack rate in the infectivity control group (i.e. group exposed to pathogen, but not receiving the vaccine) is required to achieve this power. With a 80% attack rate and equal number of subjects ( $n=10$ ), the power to detect an estimated 50% efficacy is reduced to 63%. Therefore, we aim in this study to achieve a 100% attack rate in 10 subjects.

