In the first controlled human *Schistosoma mansoni* Infection (CoHSI) study that took place between 2016-2018, we successfully developed a male-only controlled human *Schistosoma mansoni* infection model (trial name: CoHSI1 study). In total 17 healthy volunteers were exposed to increasing doses of male cercariae. Controlled infection with 20 male *Schistosoma mansoni* cercariae was safe and well-tolerated, and had a high attack rate (82%) [11]. In analogy, this subsequent study aims to establish a female-only controlled human *Schistosoma mansoni* infection (CoHSI) model.

The sex of the worms has been hypothesised to differentially impact host immune responses. In contrast to males that trigger strong innate immune responses, females are found to dampen innate immune reactions resulting in improved parasite survival [12]. This makes female worms an important vaccine target. Not only would the establishment of a female-only CoHSI model allow exploration of sex-specific immune responses, but also it may be used to provide early proof-of-concept data on candidate schistosomiasis vaccines. This is of particular relevance as one of the developed schistosomiasis vaccine candidate's target antigens is preferentially expressed on female schistosomes.

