### 3. STUDY DESIGN

This study is an open label, dose escalation intervention trial with an adaptive design.

Volunteers will be exposed to predefined doses of cercariae in groups of three and subsequently seven volunteers. Dose escalation will be performed according to the schedule depicted in figure 1. If all three volunteers in one group show detectable circulating anodic antigen in serum, seven additional volunteers will be exposed to the same dose. If not all volunteers in one dose group become infected, the next group of three volunteers will be exposed to a higher dose. The highest dose is 60 cercariae. If one or more volunteers from group A of 60 cercariae have a positive CAA test, another seven volunteers will also be exposed to this dose (group B). If both group A and group B volunteers (total 10) were exposed to the same dose, the study will stop.

[figure not shown]

Figure 1. Dose schedule. In case all volunteers become positive for *Schistosoma* circulating anodic antigen, the additional volunteers will be exposed to the same cercariae dose (green arrows, continue from group A to B). In case not all volunteers become positive for *Schistosoma* circulating anodic antigen, the dose will escalate (red or yellow arrows).

In the clinical study performed earlier we exposed four groups to male cercariae. The starting dose for the first group (A1) was also 10 cercariae. After dose-escalation to 30 cercariae for the second group (A2), we decided to dose de-escalate and expose the third group (A3) to 20 cercariae because of the burden of severe adverse events related to acute schistosomiasis syndrome in one of the volunteers (please refer to paragraph 11.3 or the Product Dossier section 2.3.2: Human exposure" for more information). The last cohort was then also exposed to 20 cercariae (B). We have thus adjusted the dose escalation schedule to allow for slower escalation if needed.

In addition, we have included cercarial doses that are higher than those used in the male cercariae infection study. This has been done for two reasons: 1) rodent experiments suggest that female cercariae may be less likely to establish infection as worm counts rendered fewer numbers in single-sex female infected animals when compared to single sex male infected animals; and 2) because female worms do not fully mature if they are unable to mate, CAA levels are expected to be lower than in mixed or single-sex male infections.

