#### 10.1.2 Attack rate per dose group

The attack rate will be calculated by division of the number of volunteers with female *Sm* infection by the total number of volunteers in the per protocol analysis, multiplied by 100% (e.g. POS/TOTAL subjects \* 100%). Volunteers withdrawing from the trial procedures at any time after infection and before the end of the study, will be tabulated as positive and included in the per protocol analysis if they had a serum CAA  $\geq 1$  pg/mL at any timepoint after exposure and before praziquantel treatment. They will be excluded from the analysis if there was no positive serum CAA sample until the moment of withdrawal.

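### Section 4.4's ±22.5% assumes a fixed 10 volunteers at a dose; below 60 cercariae, seven of the 10 are added only after 3/3 positive, so the figure does not describe the per-dose attack rate

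*Protocol*

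**What the plan says.** Section 4.4 sets the aim: "we aim in these studies to achieve a 100% infection rate in 10 subjects". It then gives a precision for a less favourable case. "At a lower infection rate of 80% (for example"), it states, "this sample size will estimate attack rate with precision of approximately" ±22.5%, which it glosses as "ruling out an attack rate of less than 50" per cent. The section does not mention stages.

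Section 3 describes a two-stage rule at each dose: "If all three volunteers in one group show detectable circulating anodic antigen in serum, seven additional volunteers will be exposed to the same dose". If any of the three is negative, the next three volunteers get a higher dose. The highest dose, 60 cercariae, has its own rule: one or more positives among the first three is enough to add seven. Section 3 also says that the study stops once 10 volunteers have had the same dose.

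Section 10.1.2 defines the estimate for each dose group as a raw proportion: "The attack rate will be calculated by division of the number of volunteers with female" infection by the total in the per-protocol analysis.

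**The concern.** The attack rate is part of the primary objective, and ±22.5% is the only precision the protocol gives for it. A reader will take it as what the trial delivers for a dose with an 80% attack rate. Below 60 cercariae, however, the number exposed at a dose depends on the first three results, and those results then enter the estimate. This has two effects. A dose may be left with three volunteers, whose results say very little. If it does reach 10, three of them are positive by selection and the raw rate runs high. Section 4.4 states neither effect, although this rate is meant to inform the choice of a dose for later vaccine studies.

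**Working it through.** **Inputs.** Group sizes 3 and 7 and both expansion rules (Section 3); 80% example, n = 10 and ±22.5% (Section 4.4); raw rate per dose (Section 10.1.2); 82% attack rate with 20 male cercariae (Section 1). Assumptions: 95% two-sided intervals, since Section 4.4 gives no confidence level for the precision, and independent volunteers without withdrawals.

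**1. The plan's own figure.** Wilson interval for x of n with z = 1.96: centre (x + z²/2)/(n + z²), half-width z/(n + z²) × √(x(n − x)/n + z²/4).
- For 8/10: centre (8 + 1.92)/13.84 = 71.7%; half-width 1.96/13.84 × √(1.6 + 0.96) = 22.7 points; interval 49.0% to 94.3%.
- This matches ±22.5% and a lower limit of about 50%. The printed figure is sound for a fixed sample of 10.

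**2. Chance that a dose gets 10 volunteers.** With true attack rate p:
- Below 60 cercariae it is p³. At 80%: 0.8³ = 51.2%, so 48.8% stay at three. At 82%: 0.82³ = 55.1%, so 44.9% stay at three.
- At 60 cercariae it is 1 − (1 − p)³. At 80% the dose misses 10 in 0.2³ = 0.8% of cases.

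**3. Precision if the dose stays at three (below 60).** The best result is 2/3. Wilson: centre (2 + 1.92)/6.84 = 57.3%; half-width 1.96/6.84 × √(0.667 + 0.960) = 36.6 points; interval 21% to 94%. The exact interval is 9% to 99%. Neither rules out a rate below 50%.

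**4. Average raw rate in each branch (below 60).** After 3/3 the count is 3 + Binomial(7, p), so the mean is (3 + 7p)/10. If the dose is left at three, the mean is (p − p³)/(1 − p³).

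| True rate | Reaches 10, below 60 | Stays at 3, below 60 | Mean raw rate if 10 | Mean raw rate if 3 | Misses 10 at 60 cercariae |
|---|---|---|---|---|---|
| 50% | 12.5% | 87.5% | 65% | 43% | 12.5% |
| 70% | 34.3% | 65.7% | 79% | 54% | 2.7% |
| 80% | 51.2% | 48.8% | 86% | 59% | 0.8% |
| 90% | 72.9% | 27.1% | 93% | 63% | 0.1% |

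At 60 cercariae and a true 80%, the mean given 10 volunteers is 80.2%, so the bias there is negligible.

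**5. What an observed 8/10 rules out.** At a true 50%, the chance of 8 or more of 10 is 56/1024 = 5.5% in a fixed sample. Given expansion below 60, it is the chance of 5 or more of 7, which is 29/128 = 22.7%. Before the gate is passed it is 0.125 × 0.227 = 2.8%.

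**6. Whether the trial ends with some dose at 10.** This fails only if the trial reaches 60 cercariae and all three volunteers there are negative, so its chance is at most (1 − p)³ for the rate p at 60. For an assumed ladder of true rates 0.3/0.5/0.7/0.82/0.9, it is 0.973 × 0.875 × 0.657 × 0.449 × 0.001 = 0.03%.

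**7. Does pooling across doses help?** The rule was simulated for assumed doses 10/20/30/40/60 (only 10 and 60 are in the readable text) and true rates 0.3/0.5/0.7/0.82/0.9, 0.5/0.7/0.82/0.9/0.98 and 0.7/0.82/0.9/0.95/0.98. Trials that used at least two doses were kept. Firth-penalised logistic regression on log dose cut the root mean squared error at doses left at three from about 0.25 to 0.15–0.20. It cut the upward bias at the dose with 10 from 4–7 points to under 2.

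**The case against.** The strongest reply is that Section 4.4 describes the final group of 10, and the design does deliver one. Because one positive of three is enough at 60 cercariae, the trial ends without a group of 10 only if the top dose gives 0/3. This stands. A reader might infer that the trial often fails to reach 10 volunteers at any dose; the documents do not support that. The shortfall belongs to a given dose below 60.

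A reader might also infer that the gate undermines the target, "Therefore, we aim in this study to achieve a 100% attack rate in 10 subjects". It does not. One negative in the first three already makes 10/10 impossible, so escalating loses nothing for that target, and a dose with a true 100% rate always reaches 10. Section 4.4 also words it as an aim.

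A third tempting step is to compute the chance that the trial finds any 10/10 dose, and to conclude that ending without one is likely or that a better, higher dose is never tried. That depends on Figure 1, which is not shown, and on the stop rule, where the protocol is not consistent. Section 3 stops the study once 10 have had one dose. Section 9.5 escalates after a group with fewer than 100% infected and says that this may be a group of 3 or of 10. No trial-level figure of that kind can be relied on.

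Finally, the gate does not make a misleading 8/10 more common overall (2.8% against 5.5% at a true 50%), and a dose-response model could be left to an analysis plan. Both are fair. The inflation arises once a dose has been expanded, which is how the result will be read. The regression is a supportive addition; leaving it out is not an error in itself.

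**Conclusion.** The concern holds for doses below 60 cercariae. The ±22.5% is arithmetically right for a fixed 10 but is not a property of the per-dose estimate under the 3 + 7 rule. At a true 80%, a given dose below 60 stays at three volunteers in 49% of cases, with a half-width of about 37 points at best. In the other 51% the raw rate is on average 6 points too high; at a true 50% it is 15 points too high. At 60 cercariae the stated figure is close to correct. The single-dose results rest only on independent volunteers, no withdrawals and 95% intervals; they do not depend on Figure 1 or on the stop rule. The simulated gain from regression does depend on the assumed doses and rates. This calls for a correction to the sizing text and one inexpensive analysis. It is no case against the escalation scheme.

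**What to change.** 1. **Section 4.4.** Say that ±22.5% applies to a fixed sample of 10. Add that a dose below 60 cercariae reaches 10 with probability p³ (51% at 80%) and otherwise rests on three volunteers, that 60 cercariae has a different gate, and that the raw rate after a 3/3 gate is biased upward (86% on average at a true 80%). A short table like the one above is enough.
2. **Section 10.1.2.** Keep the raw rate per dose. Add, as a supportive estimate, one Firth-penalised logistic regression of antigen positivity on log dose, using all exposed volunteers, with intervals at each tested dose.
3. **Sections 3 and 9.5.** Reconcile the two statements on what follows a group of 10. Which one is intended is for the investigators to say.

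The cost is protocol wording and one regression on data already collected, with no extra volunteers or procedures and no change to the escalation rule. The downsides are a less favourable stated precision and a model that assumes a monotone logistic dose-response. The model also adds nothing if the first dose is expanded and the study stops there, because the slope cannot then be estimated.

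### Section 4.4: with 8 of 10 infected, the stated precision of about ±22.5% does not rule out an attack rate below 50%

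*Protocol*

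**What the plan says.** Protocol section 4.4 sets the target: "we aim in these studies to achieve a 100% infection rate in 10 subjects". It then gives a fallback example, an infection rate of 80%, and says that "this sample size will estimate attack rate with precision of approximately" ±22.5%, which it translates into "ruling out an attack rate of less than 50" per cent. Neither the type of interval nor the confidence level is given for this figure. The two-tailed alpha of 0.05 later in the section belongs to the power statement for future vaccine studies.

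Section 10.1.2 defines the attack rate as the observed proportion, positives over total, and states no interval. Section 4.4 is therefore the only place in the protocol that says how precisely this main endpoint will be known.

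**The concern.** The sentence has two parts: a half-width, and a conclusion drawn from it about 50%. The second does not follow from the first. Read literally, 80 − 22.5 = 57.5, so a symmetric ± would give a limit of 57.5% and not 50%. If the interval is asymmetric, as most small-sample binomial intervals are, the lower limit has to be worked out, and it falls below 50% for nearly every usual method.

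What is at stake is the interpretation of a result that the protocol itself treats as plausible. A reader who relies on section 4.4 would take 8/10 as evidence that the true attack rate is at least 50%. The data would not support that at the conventional level.

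**Working it through.** **Inputs.** n = 10 and an 80% infection rate, i.e. x = 8 (section 4.4). Confidence level: not stated; 95% two-sided assumed, with 90% tried as an alternative. The ten are treated as a simple binomial sample, as section 4.4 does.

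**Reproducing ±22.5%.**

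- Wald: 1.96 × √(0.8 × 0.2 / 10) = 0.248, giving 55.2% to 104.8%. The half-width is 24.8 points. Cut at 100%, the interval is 55.2% to 100%, and half its length is 22.4.
- Wilson, with z² = 3.84: centre = (0.8 + 3.84/20) / (1 + 3.84/10) = 0.717; half-width = 1.96 × √(0.016 + 3.84/400) / 1.384 = 0.227. The interval is 49.0% to 94.3%.

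So the stated figure is recovered approximately by Wilson (22.7), and also by a Wald interval cut at 100% (22.4).

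**Does 8/10 exclude rates below 50%?** 95% two-sided intervals:

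| Method | Lower | Upper | Half-width | Lower limit at or above 50%? |
|---|---|---|---|---|
| Wald (cut at 100%) | 55.2 | 100 | 22.4 | yes |
| Jeffreys | 49.7 | 95.6 | 22.9 | no |
| Wilson | 49.0 | 94.3 | 22.7 | no |
| Mid-p | 48.0 | 96.5 | 24.2 | no |
| Agresti-Coull | 47.9 | 95.4 | 23.7 | no |
| Logit | 45.9 | 95.0 | 24.5 | no |
| Clopper-Pearson (exact) | 44.4 | 97.5 | 26.5 | no |
| Wilson, continuity-corrected | 44.2 | 96.5 | 26.1 | no |

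**Direct test of 50%.** P(X ≥ 8 | n = 10, p = 0.5) = (45 + 10 + 1)/1024 = 56/1024 = 0.055. This exceeds 0.025, and also 0.05. The exact one-sided 95% lower bound is 49.3%.

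**Why the Wald result cannot be relied on.** Its lower limit passes 50% as soon as x = 8 (at x = 7 it is 70 − 28.4 = 41.6%). If the true rate were exactly 50%, it would therefore wrongly exclude 50% on this side with probability 0.055, more than twice the nominal 0.025.

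**Would a 90% level rescue the sentence?** At 90%, Wald (from 59.2%), Wilson (54.1% to 93.1%), Agresti-Coull (from 53.3%), mid-p (from 53.3%) and Jeffreys (from 54.8%) clear 50%. Their half-widths are 19.5 to 20.8, which do not match 22.5. The exact 90% interval is 49.3% to 96.3% (half-width 23.5) and does not clear 50%.

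**What would exclude 50%.** For 9/10, P(X ≥ 9 | p = 0.5) = 11/1024 = 0.011, and the exact 95% interval is 55.5% to 99.7%.

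**Context.** For 10/10 the exact two-sided 95% lower limit is 0.025^(1/10) = 69.2%.

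**The case against.** Several points on the other side are sound.

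- **A reader might infer that ±22.5% is itself a miscalculation.** It is not. The text says it is approximate, and the Wilson half-width is 22.7.
- **One reading makes the whole sentence coherent:** a Wald interval cut at 100% gives 22.4 and a lower limit of 55.2%. That stands as a possible origin. It does not rescue the claim, because at n = 10 that limit has about twice its nominal error rate at 50%.
- **A reader might treat the exact limit of 44.4% as the only correct one.** The protocol does not commit to Clopper-Pearson. Under Wilson, which also matches the stated half-width, the miss is one point.
- **A reader might infer that section 4.4 mistakes an observed 10/10 for a true rate of 100%.** The text does not say so. "Therefore, we aim in this study to achieve a 100% attack rate in 10 subjects" states a target in a sample, section 10.1.2 defines the attack rate as an observed proportion, and no limit is given for 10/10. The 69% figure is useful context for vaccine-trial planning and does not show an error.
- **The practical reach is small.** The 80% is an example. Escalation and expansion (sections 3 and 9.5) depend on whether all volunteers, or at the top dose any, become positive. No rule or planned analysis uses 50% or ±22.5%.

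What remains is the conclusion about 50%, which the protocol states and the figures do not support.

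**Conclusion.** The inference that 8/10 rules out an attack rate below 50% is wrong as written. At 95% it fails by about 1 point under Wilson and about 6 points under the exact method; it holds only under Wald. The half-width of about 22.5 can stand as an approximation once its method is named. This is a correction to one sentence, but that sentence is the protocol's only precision statement for a main endpoint.

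The conclusion assumes a 95% level and a simple binomial sample of ten. Below the top dose the ten arise in two steps: "If all three volunteers in one group show detectable circulating anodic antigen in serum, seven additional volunteers will be exposed to the same dose". A reader might infer that this makes the claim weaker still, but the direction depends on the conditioning. At a true rate of 50%, at least 5 of the next 7 are positive with probability 29/128 = 22.7% among doses that have passed 3/3. Counting all doses tried, the probability is 1/8 × 29/128 = 2.8%. The point does not rest on either figure.

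**What to change.** In section 4.4:

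1. Name the interval method and the confidence level.
2. Delete the statement that rates below 50% are ruled out.
3. Give the actual interval for 8/10: for example Clopper-Pearson 95%, 44% to 97%, or Wilson 95%, 49% to 94%.
4. Add that at least 9/10 would be needed to exclude 50% (exact 95% interval 55.5% to 99.7%).
5. Optionally, add that 10/10 has an exact 95% lower limit of 69%, as context for carrying the dose into vaccine-trial planning.

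The cost is a text correction and a slightly less favourable precision statement. Group sizes, escalation rules and conduct are unchanged.

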### 10.2 Other study parameters

Delays in the time to positive serum or urine CAA test will be examined using Kaplan-Meier plot and log-rank (Mantel Cox) test, whereby different dose groups or a historical comparison with the male *Sm* cercariae infection will be made.

In the exploratory immunological analyses we will assess differences by comparing mean values between the dose groups or the infected/uninfected individuals using either a two-tailed student's t-test or non-parametric equivalents, paired if pre-infection values are compared with post-infection values, unpaired if comparisons are made between independent groups. For categorical variables (e.g. the number of positive assays), the chi-squared test or Fisher's exact test will be used (two-tailed). Similar to the CAA kinetics, historical comparison with the male *Sm* cercariae infection will be made.

To compare the metabolic changes after infection targeted metabolomics and changes in the microbiome, a straightforward multivariate analysis with a more general screen and multivariate modeling with principal component analysis (PCA) and partial least square

(PLS) analysis will be used. Also specific approaches for the time-resolved analysis will be used, multilevel analysis and/or (ANOVA)-simultaneous component analysis (ASCA).

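### Section 4.4 states 63% power for 50% efficacy at an 80% attack rate; on its own inputs (80% v 40%, 10 per group, two-sided 5%) the power is about 44%

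*Protocol*

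**What the plan says.** Protocol section 4.4 (Sample size calculation) gives two power figures for a future vaccine study that uses this infection model.

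- Reference case: it says "small groups of roughly 10 subjects are generally preferred", "allowing for detection of roughly ~50% protective vaccines with a power of 80" per cent, at a two-tailed alpha of 0.05. It adds that "A 100% attack rate in the infectivity control group" is needed to reach this power.
- Reduced case: with an 80% attack rate and 10 subjects in each of two equal groups, "the power to detect an estimated 50% efficacy is reduced to 63" per cent.

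The section then concludes that this trial should aim for a 100% attack rate in 10 subjects. It names no test for either figure, and it gives no attack rate for the vaccinated group.

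**The concern.** Vaccine efficacy is the relative reduction in attack rate. At a 100% control attack rate, 50% efficacy is 100% v 50%, and the relative reduction and the percentage-point difference are both 50. At 80% they separate: 50% efficacy is 80% v 40%, a difference of 40 points. A fall in power from 80% to only 63% looks too small for that change.

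The reduced case is realistic. Section 1 reports an 82% attack rate for 20 male cercariae. Section 3 allows the top dose to be expanded to 10 volunteers when only one of the first three is positive, so the trial can finish below 100%. Whoever then judges whether the model is good enough for vaccine testing would read in section 4.4 that 63% power remains.

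**Working it through.** **Inputs, all from section 4.4:** 10 per group, equal groups; two-sided alpha 0.05; efficacy 50%; control attack rate 100% or 80%. Assumptions, because the section does not say: efficacy is a relative reduction, and there is no dropout.

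**Formula.** Pooled-variance normal approximation, with control rate p1, vaccine rate p2, p̄ = (p1 + p2)/2 and n = 10:

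power = Φ{ [ |p1 − p2| − 1.96·√(2p̄(1 − p̄)/n) ] / √( [p1(1 − p1) + p2(1 − p2)]/n ) }

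**Step 1: the reference figure.** 100% v 50%, p̄ = 0.75.
- Null term: 1.96 × √0.0375 = 0.380. Alternative SE: √0.025 = 0.158.
- Φ[(0.500 − 0.380)/0.158] = Φ(0.76) = **77.7%**.
- Uncorrected chi-square, exact power: 10/10 v 6/10 is significant and 10/10 v 7/10 is not, so power = P(Bin(10, 0.5) ≤ 6) = 848/1024 = **82.8%**.

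These two values bracket 80%, so the reference figure is reproduced.

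**Step 2: the disputed figure.** 80% v 40%, p̄ = 0.60.
- Null term: 1.96 × √0.048 = 0.429. Alternative SE: √0.040 = 0.200.
- Φ[(0.400 − 0.429)/0.200] = Φ(−0.15) = **44.2%**, against the stated 63%.

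Other two-sided methods for 80% v 40%:

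| Method | Power |
|---|---|
| Unpooled z | 51.6% |
| Likelihood ratio | 48.4% |
| Arcsine | 47.2% |
| Uncorrected chi-square, mid-p, Barnard, Boschloo | 42.5% |
| Continuity-corrected z | 25.9% |
| Fisher's exact, Yates chi-square | 25.3% |

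The test-based rows, from likelihood ratio to Fisher, come from full enumeration of the two binomials. The highest value is still 11 points short of 63%.

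**Step 3: where 63% does appear.** 80% v 30%, p̄ = 0.55.
- Null term: 1.96 × √0.0495 = 0.436. Alternative SE: √0.037 = 0.192.
- Φ[(0.500 − 0.436)/0.192] = Φ(0.33) = **63.0%**.

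The efficacy in that comparison is 1 − 30/80 = 62.5%, not 50%.

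**Step 4: sensitivity to the test.** Fisher's exact test for 100% v 50%: 10/10 v 5/10 gives p = 0.033 and 10/10 v 6/10 gives p = 0.087, so power = P(Bin(10, 0.5) ≤ 5) = 638/1024 = 62.3%. For 80% v 40% it is 25.3%.

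**Step 5: what the reduced case would need.** By the pooled normal formula, 80% power for 80% v 40% takes 23 per group.

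**The case against.** The strongest reply is that the sentence is illustrative. It concerns a future study that has not been designed and would have its own calculation. It sets neither the group sizes nor any rule here, and the correction helps the protocol's argument: if power falls to 44% rather than 63%, a 100% attack rate is wanted all the more. This stands, and it limits the weight of the point. It does not make the number right.

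A reader might infer more than the documents support:

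- **That the 80% figure is also wrong.** It is hedged with roughly, and 77.7% and 82.8% lie on either side of it. It fails only under Fisher's exact test.
- **That Fisher's exact test is the protocol's test for the vaccine comparison.** Section 4.4 names none. Section 10.2 says "the chi-squared test or Fisher's exact test will be used (two-tailed", but this is for categorical variables in this trial's exploratory analyses, and it allows either test. With 2.5 uninfected expected per group in the 100% v 50% case, an exact test is a sensible preference, but it remains a preference.
- **That the cause is established.** The match to 80% v 30% is close, and one formula then accounts for both printed figures, but the protocol shows no working. Other routes land nearby. For 80% v 40%, a one-sided unpooled z gives 63.9% and a one-sided chi-square 61.4%, but both contradict the stated two-tailed level. Two-sided Fisher for 100% v 50% gives 62.3%, but that is the other scenario. None of these rescues the figure.
- **That n = 10 loses its only support.** Section 4.4 also gives a precision argument for 10 subjects, which this point does not touch.
- **That a later vaccine trial will be underpowered.** That would require the sentence to be reused without a fresh calculation, and nothing in the protocol says it will be.

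**Conclusion.** The 63% is wrong on the inputs that section 4.4 itself states. The power for 50% efficacy at an 80% control attack rate, with 10 per group and a two-sided 5% level, is about 44% by the approximation that also gives about 78% for the reference case. The overstatement is about 19 percentage points (63 − 44.2 = 18.8). Across the two-sided methods tried, the range is 25% to 52%.

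The conclusion rests on reading efficacy as a relative reduction and on no dropout. If a 50-point absolute difference was meant, 63% is right for 80% v 30%, but calling it 50% efficacy is then wrong, so the sentence needs correction either way.

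The correction should be made but is not critical: the figure is a stated premise for the 100% target, yet nothing in the conduct or analysis of this trial depends on it.

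**What to change.** In section 4.4:

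1. Replace 63% with about 44%, and state the compared rates (80% v 40%).
2. Name the test or approximation behind both power figures. The roughly 80% may stay if the normal approximation or the uncorrected chi-square is given as its basis.
3. Add that with Fisher's exact test the powers would be about 62% (100% v 50%) and 25% (80% v 40%).

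Possible wording: *With 10 subjects per group and a two-sided 5% level, power for 50% efficacy is about 78% at a 100% control attack rate (100% v 50%) and about 44% at an 80% attack rate (80% v 40%), by the pooled normal approximation; with Fisher's exact test these become about 62% and 25%.*

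The cost is a change of text. The stated figure becomes less favourable, enrolment and decision rules stay as they are, and the argument for a 100% attack rate becomes stronger.
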